**Interviewer:**

**→** I would now like to ask you about the ways in which you have made money. I will first ask you about wage jobs you may have had (where you worked for someone else for pay) and later I will ask you about any businesses you may own or co-own.

| **No.** | **Questions and Filters** | **Coding Categories** | **Codes** | **Skip to:** | **VARIABLE** |
| --- | --- | --- | --- | --- | --- |
| Q1601 | Did you do any work of any type for pay, profit, or barter during the last 7 days? | NO  YES | 0  1 | **Q1605** | WORK7D |
| Q1602 | Although you did not do any work during the last 7 days, do you have a job to which you will definitely return to work? | NO  YES | 0  1 | **Q1605** | RETWORK |
| Q1603 | Were you available for work during the last 7 days?  By available to work, I mean were you were physically available to work. Reasons for NOT being available to work may include being in school or being sick, disabled, or busy with household duties. | NO  YES | 0  1 |  | AVLBWK |
| Q1604 | When was the last time you did work for pay, profit or gain? | MONTHS AGO_________  YEARS AGO__________  NEVER | 00 | **Q1618**  **Q1618** | LSTWRK_M  LSTWRK_Y |
| *Interviewer:*  **→** For this set of questions, please think about any wage work you have done. By wage work, I mean work you have done for someone else for pay. Keep in mind that you may have been paid in cash or another form or payment. A an activity can be considered wage work even if it was just one time, several times, or something you do daily. Please don't include work you have done for your own business as wage work. | | | | | |
| Q1605 | Did you do any wage work during the **last 12 months**?  Remember that by wage work, I mean work for someone else for pay. You may have been paid in cash or another form or payment. Also, remember that you may have done wage work even if it was just one time, several times or something you do daily. Please don't include work you have done for your own business as wage work. | NO  YES | 0  1 | **Q1612** | WAGE30D |
| Q1606 | What kind of wage work have you done in the 1ast 12 months?  Select all that apply | DALADALA DRIVER OR CONDUDCTOR  FACTORY WORKER  TEACHER  REPAIR PERSON  SALON WORKER  TRANSPORT ITEMS  OTHER___________________ | 1  2  3  4  5  6  7 |  | WAGETP  WAGETP_S |
| Q1607 | Thinking of all the wage work you have done, how much cash did you earn from these activities, on average, over 1 month in the last year?  Probe: Think about any seasonal work you may have done. Try to account for the high and low months and do you best to identify an average monthly income from all your wage jobs. | TSH_______________  WAS NOT PAID | 99 |  | EARN30D |
| Q1608 | Did you receive any payment for this work in any other form? | NO  YES | 0  1 | **Q1610** | PAYOTHF |
| Q1609 | What would you estimate is the value of the other payments in other form that you received, on average, over 1 month in the last year? | TSH_______________ |  |  | OTHFPAY |
| Q1610 | During the last 12 months, how many weeks per month, on average did you work doing these jobs?  This should be between 0.5-4. | WEEKS______________ |  |  | WEEKPM |
| Q1611 | During the last 12 months, how many hours per week did you usually work in these jobs? | HOURS______________ |  |  | HOURPW |
| **Self-Employed**  *Interviewer:*  **→** This next set of questions is about any self-employed activities you have done. By self-employed activity, we mean you own or co-own a business and that you have invested funds in the start-up or maintenance of a business with the expectation of earning a profit. | | | | | |
| Q1612 | Did you operate any business or do any self-employed activity during the **last 12 months**?  Remember, by self-employed activity, we mean you own or co-own a business and that you have invested funds in the start-up or maintenance of a business with the expectation of earning a profit. | NO  YES | 0  1 | **Q1618** | SEMPL |
| Q1613 | What kind of business(es) do you operate?  Select all that apply.  BODA BODA  VIDEO RENTAL  FUNDI  SELL FOOD  SELL CLOTHES OR SHOES  SELL OTHER_____________  OTHER___________________ | NO  YES | 0  1 |  | B_BODA  B_VID  B_FUNDI  B_SELLFD  B_SELLCTHS  B_SELL_O  B_SELL_O_S  B_OTHER  B_OTHER_S |
| Q1614 | For the business you have been operating the longest, how long have you been operating this business? | YEARS_______________  MONTHS________________ |  |  | BUS_DURY  BUS_DURM |
| Q1615 | What were the main sources of start-up capital for your businesses?  Select all that apply.  LOAN FROM FAMILY/FRIENDS  GIFT FROM FAMILY/FRIENDS  SALE OF ASSETS OWNED  PROCEEDS FROM ANOTHER BUSINESS  OWN SAVINGS  LOAN FROM YOSEFO  LOAN FROM OTHER INSTITUTION  LOAN FROM MONEY LENDER  OTHER_____________ | NO  YES | 0  1 |  | BUS_CAP1  BUS_CAP2  BUS_CAP 3  BUS_CAP 4  BUS_CAP 5  BUS_CAP 6  BUS_CAP 7  BUS_CAP 8  BUS_CAP 9  BUS_CAP9-S |
| Q1616 | Thinking of all the businesses you have, what would you estimate to be the total value of your physical capital stock, including all tools, equipment, inputs, supplies, and finished merchandise (goods for sale)?  If your business is co-owned by other individuals, only include the portion of these items that belongs to you. | TSH________________ |  |  | CAPTL_VAL |
| Q1617 | What was your net income (profit) from your businesses on average, over a one month period in the last year? | TSH________________ |  |  | NTINCOME |
| **Credit Borrowed.**  *Interviewer:*  **→** This next set of questions is about Credit. We are interested in knowing about any cash you have borrowed from an institution. We would like you to think about the biggest loan or credit you obtained in the last 12 months for the following set of questions. | | | | | |
| Q1618 | Over the past 12 months, did you borrow cash from an institution? | NO  YES | 0  1 | **Q1631** | CRD_12M |
| Q1619 | Did you have a co-borrower on this loan? | NO  YES | 0  1 |  | CRD_CBOR |
| Q1620 | What was the source of this loan? | BANK OR OTHER INSTITUTION  INSURANCE COMPANY  YOSEFO  MONEY LENDER  EMPLOYER  RELIGIOUS INSTITUTION  OTHER NGO  OTHER__________________ | 1  2  3  4  5  6  7  8 |  | CRDSOURC |
| Q1621 | How much was borrowed? | TSH________________ |  |  | CRDBOR |
| Q1622 | Is the loan/credit re-paid in full? | NO  YES | 0  1 | **Q1624** | CRDPAID |
| Q1623 | Approximately when do you expect to pay back the money in full? | MONTH___________  YEAR___________ |  |  | CRDPAY |
| Q1624 | Total amount to be paid on the loan including interest | TSH________________ |  |  | CRDAMNT |
| Q1625 | What was the interest rate? | ____________ |  |  | INTEREST |
| Q1626 | Did you use the funds from this loan for any of the following business-related purposes?  BUSINESS INPUT  HIRE ADDITIONAL STAFF  BUILD OR REPAIR DWELLING  REPAID BUSINESS LOANS  OTHER_____________ | NO  YES | 0  1 |  | BUSEXP1  BUSEXP2  BUSEXP3  BUSEXP4  BUSEXP5_S |
| Q1627 | You said you have not yet paid this loan back in full. Did you experience any problems that made it difficult for you to pay back the loan? | NO  YES | 0  1 | **ASK ONLY IF Q1622=0** | DIFFPAY |
| Q1628 | What was the main problem you had that made it difficult for you to pay back the loan? | NOT ENOUGH MONEY TO EXPAND OUR BUSINESS  DIDN’T GET ENOUGH PEOPLE TO BUY OUR PRODUCT OR USE OUR SERVICE  SPENT MONEY INSTEAD OF SAVING IT  SOMEONE STOLE OUR PROFITS  OTHER _______________ | 1  2  3  4  5 |  | PAYPROB  PAYPROB_S |
| Q1629 | **Are you responsible for repaying any other loans including personal, family, or business loans in addition to the loan we just discussed?** | NO  YES | 0  1 |  | OTHLOAN |
| Q1630 | What is the total amount that you owe for repayment of all outstanding debts? | TSH________________ |  |  | TOTDEBT |
| **General Finance and Expenditures** | | | | | |
| Q1631 | Did you do any of the following things with your money in the past 30 days?  BOUGHT FOOD  BOUGHT CLOTHING  SPENT IT ON MY FAMILY’S NEEDS  SCHOOL FEES  SAVED THE MONEY  PAID FOR ENTERTAINMENT  BOUGHT ALCOHOL  BOUGHT CIGARETTES  BOUGHT DRUGS  GAVE MONEY FOR SEX  SPENT ON GIRL/BOYFRIEND/  CELL PHONE OR AIRTIME VOUCHER  GAVE SOME MONEY TO THE CAMP  OTHER _______________ (EXPLAIN) | NO  YES | 0  1 |  | PROFEXP1  PROFEXP2  PROFEXP3  PROFEXP4  PROFEXP5  PROFEXP6  PROFEXP7  PROFEXP8  PROFEXP9  PROFEXP10  PROFEXP11  PROFEXP12  PROFEXP13  PROFEXP14 |
| Q1632 | What would you estimate your total savings to be at this time? | TSH________________ |  |  | SAVING |
| Q1633 | How much do other individuals currently owe you? | TSH________________ |  |  | OWEDAMT |

Section 17: Closing

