**Work and Expenditures**

Questions on work and expenditures will be incorporated to assess changes in participants exposed and not exposed to the microfinance component. These questions will be derived from the Tanzania National Panel Survey’s (TNPS) Multi-topic Household Questionnaire ([W. Bank, 2012](#_ENREF_7)). Design and implementation of the TNPS is supported by the Living Standards Measurement Study-Integrated Surveys on Agriculture. Only questions relating to work and expenditures will be included.

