### 9.1.4 Mediation Sampling and Analytical Technique

In the event that program effects are identified, we will estimate path coefficients in multiple mediator models and generate bootstrapped confidence intervals for total and specific indirect effects of one or more mediator models using the Mplus program Version 6.11.([Pituch, Stapleton, & Kang, 2006](#_ENREF_65)) We will assess simple and multiple mediation in the relationships between the microfinance intervention condition, intervention mediators including hope, future orientation, social cohesion, social support, emotional distress, gender equity, conflict, alcohol and drug use, HIV stigma, perceived social support, collective efficacy, sexual relationships and risk behavior, attitudes towards HIV risk and intimate partner violence, work and expenditures, sexual relationships and risk behavior, and social and sexual network norms.

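### Total outstanding debt is asked only of men with a recent institutional loan, a group whose make-up the intervention changes

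*Protocol*

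**What the plan says.** Appendix D, Section 16 (Work and Expenditures) opens its credit block with Q1618: "Over the past 12 months, did you borrow cash from an institution". The item carries a skip to Q1631. Q1619 to Q1628 then concern the largest loan of the last 12 months, including Q1622, "Is the loan/credit re-paid in full". Two wider items close the block:

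- Q1629: "Are you responsible for repaying any other loans including personal, family, or business loans in addition to the loan we just discussed"
- Q1630: "What is the total amount that you owe for repayment of all outstanding debts"

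The items after the skip target include savings (Q1632, "What would you estimate your total savings to be at this time") and money owed to the respondent (Q1633, "How much do other individuals currently owe you"). Every man reaches these.

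Section 7.5 gives the purpose of the section: "Questions on work and expenditures will be incorporated to assess changes in participants exposed and not exposed to the microfinance component". Section 9.1.4 includes it among the mediators: "attitudes towards HIV risk and intimate partner violence, work and expenditures, sexual relationships and risk behavior, and social and sexual network norms". Section 7.5 has mediators measured at baseline, 12 and 30 months. Section 6.5 applies the baseline procedures at follow-up, and Section 8.2.3 says the survey form is used at all three waves. Section 5.2.6 funds up to three loan cycles for intervention camp members. Under Section 5.4, control camps receive only an HIV prevention session after month 30. Section 10.5.2 names indebtedness as a possible harm of taking a loan.

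**The concern.** Q1629 and Q1630 are worded to cover any debt, but they sit behind a gate that admits only recent institutional borrowers. A man who owes only his family, or only a balance on an institutional loan taken more than 12 months ago, leaves the block with no debt recorded. What he has saved and what others owe him are still asked.

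The gate would matter less if it opened equally often in both arms. Here the intervention consists in part of institutional loans, so passing the gate after baseline is a consequence of allocation. Neither obvious handling of the gap gives an as-randomised comparison of total debt:

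- Analysing only men with a Q1630 value compares borrowers selected differently in the two arms.
- Setting skipped men to zero is right only if they owe nothing. A man who swaps a family loan for an equal institutional loan would appear to move from no debt to debt.

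What is at stake is one work-and-expenditures measure and a comparative view of a risk that the protocol itself names.

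**Working it through.** **Routing.** The extracted text does not tie the skip at Q1618 to a response. Only NO fits, because Q1619 onward presupposes a loan.

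| Answer to Q1618 | Items reached | Total debt (Q1630) |
| --- | --- | --- |
| YES | Q1619 to Q1630, then Q1631 to Q1633 | recorded, including informal and older debt |
| NO | Q1631 to Q1633 only | never asked |

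No other survey item gives the skipped men an outstanding balance. Q1615 mentions family, friend and money-lender loans, but only as yes/no sources of start-up capital for men who ran a business, without an amount.

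**Size.** The plan states no figure to reproduce. The documents give the number of men (1249, Protocol Summary) and attrition (20%, Section 9.1.1). All uptake and debt shares below are assumptions.

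Men per arm: 1249 / 2 × 0.8 = 499.6, about 500.

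Let u be the share passing Q1618, p the true prevalence of informal debt (equal in both arms, so no real difference), and r the prevalence of informal debt in institutional borrowers relative to other men. Prevalence in non-borrowers is p / (r·u + 1 − u). With zero-filling, only borrowers' informal debt is seen, so

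recorded share = u·r·p / (r·u + 1 − u), which is u·p when r = 1.

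*Month 12*, with u = 0.30–0.70 (intervention) and 0.02–0.10 (control):

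- Men with a Q1630 value: 500 × 0.30 = 150 to 500 × 0.70 = 350, against 500 × 0.02 = 10 to 500 × 0.10 = 50.
- With r = 1 and p = 10%, informal debt is captured for 3.0–7.0% against 0.2–1.0%.
- The smallest spurious difference pairs u = 0.30 with 0.10; the largest pairs 0.70 with 0.02.

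| p | r | Smallest (points) | Largest (points) |
| --- | --- | --- | --- |
| 5% | 1 | 1.0 | 3.4 |
| 10% | 1 | 2.0 | 6.8 |
| 20% | 1 | 4.0 | 13.6 |
| 10% | 0.5 | 0.015/0.85 − 0.005/0.95 = 1.24 | 0.035/0.65 − 0.001/0.99 = 5.28 |
| 10% | 2 | 0.06/1.30 − 0.02/1.10 = 2.80 | 0.14/1.70 − 0.004/1.02 = 7.84 |

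*Month 30*, with u = 0.05–0.50 (intervention) and 0.02–0.10 (control), r = 1, p = 10%:

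- Lowest: 0.5% − 1.0% = −0.5 points.
- Highest: 5.0% − 0.2% = +4.8 points.

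These figures describe the share of men whose informal debt is captured, not the amount in shillings that Q1630 records. They illustrate the mechanism and do not estimate the bias in mean debt.

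**The case against.** The routing itself is not in dispute. The case against calling it a defect has four parts.

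1. **No planned analysis uses total debt.** It is not a named endpoint or mediator. Section 9.1.4 names only the work-and-expenditures block, and mediation is run only if program effects are found. No text proposes zero-filling, and coding of skipped items is commonly left to the SAP. This stands and limits the importance. It does not remove the gap, because no coding rule can supply answers that were never requested.

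2. **The gate matches the block's introduction**, which announces an interest in institutional borrowing. That is a fair reading of Q1619 to Q1628. It does not fit Q1629 and Q1630, whose wording goes beyond institutional loans, in a section meant to compare men exposed and not exposed to microfinance.

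3. **The named risk is covered elsewhere.** Recent study borrowers pass the gate. Repayment and default on study loans are monitored (Sections 6.8.2 and 7.6.2), and borrowers are asked about harm and repayment difficulty (Section 7.6.1). Q1618 with Q1622 still compares the arms on an unpaid largest recent institutional loan. Q1620 lists money lenders and employers, so some of those loans may pass the gate. All this stands; the clearest loss is debt to family and friends. Study-loan monitoring, however, does not show family debt and has no control counterpart. A man who failed on an early loan and has not borrowed from an institution in the 12 months before month 30 answers NO, and the survey records none of his debt.

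4. **The follow-up form is not shown.** Appendix D lacks some items that Section 7 describes, such as moral agency, so the fielded follow-up form must differ in places. Section 8.2.3 supports the same routing at each wave but does not prove it. This lowers confidence.

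**Conclusion.** The concern holds, at minor severity and with medium confidence. As printed, the survey cannot give total debt by randomised arm after baseline, because the men who skip Q1630 are never asked and who skips depends on the loans the intervention provides. This rests on the skip belonging to NO, the only coherent reading, and on the same routing at 12 and 30 months, which is inferred from Sections 6.5 and 8.2.3.

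The documents fix neither size nor direction. Under the assumed shares the spurious difference in recorded informal debt at month 12 runs from 1.0 to 13.6 points across the scenarios shown, and at month 30 it could take either sign. The STI and violence analyses and the named secondary endpoints are not affected.

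**What to change.** For the 12- and 30-month surveys, route Q1618 = NO to Q1629 and Q1630 instead of Q1631. For these men, drop the closing reference in Q1629 to a loan already discussed, so that it asks about any loans. Compare total debt by randomised arm in all surveyed men. Keep Q1618 with Q1622 for unpaid recent institutional loans, and the repayment database for default on study loans.

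The cost is one CAPI routing change, one reworded item, and one or two short extra questions for men who now skip them. If baseline is already complete, there is no ungated baseline value, so the comparison is post-baseline only. For any wave already collected under the present routing, Q1630 should not be presented as total debt by arm.

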***Interviewer:***

→ *We have come to the end of our discussion. Thank you very much for sharing your thoughts with me. The information you have provided has been very helpful.*
